## Methods and Analysis

### Study Design

This study is a prospective single-blind randomized controlled non-inferiority trial. The Consolidated Standards of Reporting Trials (CONSORT) flowchart for enrollment and randomization is shown in Figure 1. After recruitment, participants will be contacted and will undergo in-person baseline assessment (T0) using the below-listed tests (see evaluation of the participants section and Table 1). Participants who meet the inclusion criteria will be enrolled and randomized to one of two groups: HomeCoRe and CoRe. For both the groups, the intervention will consist of a 6-week program (3 sessions/week, each lasting ~45 min). Follow-up in-person neuropsychological assessments will be scheduled at the end of the rehabilitation program (T1) and after 6 (T2) and 12 months (T3).

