### Randomization and Stratification

After baseline assessment, we will generate random numbers through the use of a computer algorithm (https://www.random.org/) from a uniform distribution in the range 0–1, dividing the range in two equal intervals and assigning each participant to the group corresponding to the sampled number (1:1 ratio), within strata defined by diagnosis (Mild or Major Neurocognitive Disorders). Neuropsychologists carrying out cognitive evaluations will be blinded to group allocation.

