### Outcome Measures

As the primary outcome measure, we will consider the change in global cognitive functioning, measured using the MMSE at T1 compared to T0. Secondary outcome measures will be longitudinal changes in all the neuropsychological tests, questionnaires and scales (T1, T2, and T3 vs. T0 when applicable according to Table 1). Secondary outcome measures will include also participant-centered outcomes to assess those aspects that are most important for the participants and the subjective evaluation of intervention success at T1.

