### Statistical Analysis

#### Sample Size Calculation

Sample size has been estimated based on previous evidence in the literature (47). Since this is a non-inferiority study, we will consider as margin *d* a value of two points difference (T1 vs. T0) at the MMSE between the two groups. We predict to obtain a mean difference between HomeCoRe and CoRe groups of about one point at the MMSE with an SD of 1. Considering an alpha significance of 0.05 and a power of 0.9, the sample size for a non-inferiority study is 18 participants per group, for a total of 36 participants. It is planned to enroll a total of 40 participants in order to account for possible dropouts. If dropout rates between T0 and T1 will be higher than expected, extra participants will be recruited. The sample size for non-inferiority studies was calculated using R 4.0.2 software, SampleSize4ClinicalTrials package.

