#### Planned Analysis

Statistical analysis on outcome measures will be conducted using the SPSS software (see Supplementary Materials for planned analysis). A normality test will be used to assess the distribution of all the outcome measures. Baseline differences between groups will then be tested using the independent samples *t*-test for parametric data and the Mann–Whitney *U*-test for non-parametric data. Within-group statistical tests will be performed for both the CoRe and HomeCoRe groups to look for significant changes in primary and secondary outcome measures over time. Between-group tests will be performed to look for differences in primary and secondary outcome measures between HomeCoRe and CoRe participants. Possible between-group differences in demographic and clinical characteristics (e.g., age, sex, years of education, diagnosis, and cognitive reserve) and in T0 scores in primary and secondary outcome measures will be considered as possible confounders and will be treated as covariates in the analysis. *p* ≤ 0.05, corrected for multiple comparisons, if appropriate, will be considered as statistically significant.

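### The trial is sized to test a 2-point MMSE non-inferiority margin, but the article's analysis section describes tests for a difference and does not link the primary analysis to that margin

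*Protocol article*

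**What the plan says.** Study Design: "This study is a prospective single-blind randomized controlled non-inferiority trial".

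Outcome Measures, on the primary outcome: "we will consider the change in global cognitive functioning, measured using the MMSE at T1 compared to T0".

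Sample Size Calculation sets the margin as "a value of two points difference (T1 vs. T0) at the MMSE between the two groups". It continues: "We predict to obtain a mean difference between HomeCoRe and CoRe groups of about one point at the MMSE with an SD of 1". With "Considering an alpha significance of 0.05 and a power of 0.9", it concludes that "the sample size for a non-inferiority study is 18 participants per group". Forty participants are to be enrolled to allow for dropout. The section does not say whether alpha is one- or two-sided, or which programme is expected to do worse.

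Planned Analysis, on the comparison of the programmes: "Between-group tests will be performed to look for differences in primary and secondary outcome measures between HomeCoRe and CoRe participants". Baseline imbalances and T0 scores are to be treated as covariates. Significance is p ≤ 0.05, corrected for multiplicity where appropriate. The section also refers to Supplementary Materials for the planned analysis. The t-test and the Mann–Whitney test are named only for baseline comparisons.

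The Discussion ties the use of HomeCoRe to whether the programmes turn out equivalent or HomeCoRe turns out less effective. It defines neither outcome.

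**The concern.** The sample size section and the analysis section address different null hypotheses. The first is built to reject the hypothesis that HomeCoRe is at least 2 points worse. The second, on its natural reading, tests whether the two programmes differ at all. The primary outcome is expressly included in that sentence, and the margin appears only in the sample size paragraph.

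Neither result of a difference test answers the trial's question. A non-significant result may only mean that the data are imprecise. A significant deficit may still lie well inside the margin. Because the article states no decision rule, p ≤ 0.05 is the only criterion it offers for the two conclusions in its Discussion. The stated 90% power belongs to a test that the analysis section does not describe.

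**Working it through.** **Inputs.** Margin 2, expected difference 1, SD 1, alpha 0.05, power 0.9 and 18 per group come from Sample Size Calculation. The 1:1 allocation comes from Randomization and Stratification. Twenty per group is the 40 enrolled with no dropout.

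**1. Reproduce the stated sample size.** With HomeCoRe 1 point worse and one-sided alpha 0.05:

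n per group = 2(z₀.₉₅ + z₀.₉₀)² × SD² / (margin − deficit)² = 2(1.645 + 1.282)² × 1² / (2 − 1)² = 17.13, so 18.

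This matches. The alternatives do not:
- one-sided 0.025: 21.01, so 22 per group;
- no true difference: 5 per group;
- HomeCoRe 1 point better: 2 per group.

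The stated figure is therefore a one-sided 5% test against the margin, with HomeCoRe assumed 1 point worse.

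**2. Compare the two tests under those assumptions.** The standard error at 18 per group is √(2/18) = 0.333. For each test the true value is 1 point from its null value (−2 or 0), so the noncentrality is 1/0.333 = 3.0 in both cases, with 34 degrees of freedom. At 20 per group the noncentrality is 3.16, with 38 degrees of freedom.

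| True deficit 1, SD 1 | 18 per group | 20 per group |
|---|---|---|
| Margin test (one-sided 5%) concludes non-inferiority | 90.2% | 92.8% |
| Difference test (two-sided 5%) is significant | 83.0% | 86.9% |
| Difference test is non-significant | 17.0% | 13.1% |

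**3. How often both occur.** If the observed SD is 1 at 18 per group, the difference test is significant for an observed deficit above 2.032 × 0.333 = 0.68 points. The margin test succeeds for an observed deficit below 2 − 1.691 × 0.333 = 1.44 points. Any deficit between these values satisfies both. In 200,000 simulated trials at 18 per group, 73.3% met the margin and also showed a significant difference, and 90.1% met the margin. So 73.3/90.1 = 81% of the trials that met the margin also gave a significant result.

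**4. The other direction.** Suppose a non-significant result were read as comparability, and HomeCoRe were truly 2 points worse. The noncentrality is 2/(SD × 0.333). The plan gives only SD 1; the larger values are assumptions, shown as a range.

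| SD of change | Difference test non-significant, 18 per group | 20 per group | Margin test wrongly succeeds |
|---|---|---|---|
| 1 (plan) | under 0.01% | under 0.01% | 5% |
| 2 | 17% | 13% | 5% |
| 3 | 51% | 46% | 5% |
| 4 | 69% | 66% | 5% |

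**5. Effect of the confidence level.** A two-sided 90% interval corresponds to one-sided 5% and keeps the 90.2%. A two-sided 95% interval corresponds to one-sided 2.5%, and power becomes 83.0% at 18 per group and 86.9% at 20. Reaching 90% would then need 22 per group, 44 in total.

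All percentages are for an unadjusted t-test. The planned covariates would change the exact values but not which hypothesis is tested.

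**The case against.** The strongest reply is that the article is a summary and points to Supplementary Materials that could contain a margin-based analysis. A reader might infer from the article that the margin plays no part anywhere in the plan. The documents do not support that, because the supplement cannot be seen. What stands is narrower: the article does more than leave the point open. It describes an approach for the primary outcome that does not fit its own sample size, and it would also not fit a supplement that used the margin.

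Second, no between-group outcome test is named, and the sentence covers many measures that have no margin. The p ≤ 0.05 threshold could be applied to a margin-shifted test. It is therefore too much to say that one identical test is fixed for every outcome, and the null of zero difference is inferred from the wording. It remains the natural reading, and nothing in the section points to the margin.

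Third, a reader might infer that the plan would accept HomeCoRe on a non-significant result. No section says so. The false-acceptance figures are therefore conditional on that reading. At the plan's own SD of 1 that error is negligible, and the larger figures rest on SDs that the article does not give.

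Fourth, the one-sided 5% level and the direction of the expected difference are back-calculated from 18 per group, not stated. That is correct, and it affects the wording of the fix.

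**Conclusion.** The concern holds in this form: the article declares and sizes a non-inferiority trial, but its analysis section describes difference tests on the primary outcome and does not connect them to the 2-point margin. This is a conflict within the article, not an omitted detail, and it should be corrected before analysis because it determines whether the primary question is answered.

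The main consequence needs no assumption beyond those that reproduce 18 per group. If the sponsor's prediction is right, the difference test is significant in 83.0% of trials although the margin test succeeds in 90.2%. The usual result would be a significant HomeCoRe deficit in a trial that met its margin, with no stated rule for interpreting it. The risk of taking a full 2-point deficit for comparability is secondary: it arises only if non-significance is read as success and the SD is well above 1.

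**What to change.** In Planned Analysis, separate the primary outcome from the general sentence and state:

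- The HomeCoRe minus CoRe difference in T1–T0 MMSE change, with the covariate adjustment already planned, will be estimated with a two-sided 90% confidence interval (one-sided 5%).
- Non-inferiority is concluded only if the lower limit is above −2; otherwise it is not shown.
- A non-significant difference test is not evidence of non-inferiority. Any difference test on the primary outcome is supplementary.

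In Sample Size Calculation, state that alpha is one-sided and that HomeCoRe is assumed 1 point worse. If the supplement already contains a margin-based rule, bring the article's text into line with it.

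With the 90% interval the cost is wording only: no new data and no change in sample size. If a 95% interval is chosen, restate power as about 83% at 18 per group (87% at 20), or plan for 22 per group, which is 44 in total against the 40 now planned.

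### Covariates for the primary MMSE comparison appear to be chosen by observed baseline imbalance; T0 MMSE and the diagnosis stratum should be fixed in the model in advance

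*Protocol article*

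**What the plan says.** All references are to the protocol article.

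- **Outcome Measures:** the primary outcome is "the change in global cognitive functioning, measured using the MMSE at T1 compared to T0".
- **Randomization and Stratification:** allocation is 1:1 "within strata defined by diagnosis (Mild or Major Neurocognitive Disorders").
- **Planned Analysis:** "Baseline differences between groups will then be tested using the independent samples" t-test, or the Mann–Whitney test for non-parametric data. Later in the same paragraph, possible between-group differences in demographic and clinical characteristics, and in the T0 scores of the outcome measures, "will be considered as possible confounders and will be treated as covariates in the analysis". The characteristics are given as examples only: age, sex, education, diagnosis and cognitive reserve.
- **Sample Size Calculation:** "we will consider as margin *d* a value of two points difference (T1 vs. T0) at the MMSE between the two groups". The planning values are "a mean difference between HomeCoRe and CoRe groups of about one point at the MMSE with an SD of 1".

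No covariate is named as always included. T0 MMSE and diagnosis appear only as candidates under the imbalance sentence. The section points to Supplementary Materials for the planned analysis; these were not available for review.

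**The concern.** In a randomised trial a baseline difference between arms arises by chance, so a significance test cannot identify a confounder. What makes a covariate worth including is its relation to the outcome, and that is known beforehand for T0 MMSE (the outcome is change from it) and for diagnosis (the trial stratifies on it). A rule triggered by imbalance has three effects:

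- It usually omits the two variables that most deserve inclusion.
- It leaves the primary model undetermined until the baseline data are compared by arm.
- It treats an imbalance just short of the trigger as if it were none.

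The third effect matters most in a non-inferiority trial. Regression to the mean favours the arm that starts lower, so an unadjusted change score can move the estimate towards or away from the margin.

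**Working it through.** **1. The plan's own figure.** Inputs from Sample Size Calculation: margin 2, expected difference 1, SD 1, alpha 0.05, power 0.9.

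n per group = 2·SD²·(z₁₋α + z₁₋β)² / (margin − difference)² = 2 × 1 × (1.645 + 1.282)² / (2 − 1)² = 17.1, rounded up to 18. This matches the stated 18 per group and implies a one-sided 0.05 test; one-sided 0.025 would give 21.01, so 22.

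**2. How often T0 MMSE would enter.** Under randomisation a 5% baseline test is significant in about 5% of trials, so about 95% would be analysed without T0 MMSE. The 5% trigger is an assumption.

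**3. Number of candidates.** Table 1 gives 18 cognitive scores at T0 and 5 other T0 scales for all participants (ADL, IADL, BDI, SF-36, CRIq; the caregiver scale is left out because it covers only part of the sample). Age, sex, education and diagnosis bring the total to 27.

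- Expected chance differences: 27 × 0.05 = 1.35.
- P(at least one), if independent: 1 − 0.95²⁷ = 0.75.
- With 23 scores equicorrelated at an assumed 0.3, 0.5 or 0.7 plus 4 independent variables, simulation gives about 0.67, 0.56 and 0.44.
- With only 5 or 10 independent candidates: 0.23 or 0.40.

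**4. Precision.** With equal T0 and T1 variances and correlation ρ, the variance of the ANCOVA estimate relative to the change score is (1 + ρ)/2: 0.65, 0.75, 0.85 and 0.90 at ρ = 0.3, 0.5, 0.7 and 0.8. This ignores the small cost of estimating the slope. By the formula in step 1, ANCOVA would need 12, 13, 15 and 16 per arm for 90% power.

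**5. Operating characteristics.** Simulation with 18 per arm, SD of change 1, one-sided 0.05, T0 MMSE as the only candidate and p ≤ 0.05 as the assumed trigger. The article does not give ρ. Power is at a true 1-point deficit for HomeCoRe; type I error is at a true 2-point deficit.

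| ρ | Power, fixed ANCOVA | Power, test-then-adjust | Type I, fixed ANCOVA | Type I, test-then-adjust |
|---|---|---|---|---|
| 0.3 | 97% | 91% | 0.050 | 0.044 |
| 0.5 | 95% | 91% | 0.050 | 0.045 |
| 0.7 | 93% | 90–91% | 0.050 | 0.047 |
| 0.8 | 92% | 90% | 0.050 | 0.048 |

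**6. Near-miss imbalance.** Given a T0 difference Δ (HomeCoRe minus CoRe), the unadjusted change-score difference is shifted by −(1 − ρ)Δ. At ρ = 0.5 the T0 SD is 1 and the standard error of Δ is √(2/18) = 0.333. A baseline p between 0.05 and 0.20 then means |Δ| of about 0.44 to 0.68, and a shift of about 0.22 to 0.34 points against a standard error of 0.333 for the estimate itself. Such a near miss occurs in 15% of trials, half in each direction.

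| ρ | Type I, unadjusted, HomeCoRe lower | Power, unadjusted, HomeCoRe higher |
|---|---|---|
| 0.3 | 19% | 69% |
| 0.5 | 16% | 73% |
| 0.7 | 13% | 78% |
| 0.8 | 11% | 81% |

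In the same trials fixed ANCOVA keeps type I error near 5% and power at about 91–97%.

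**The case against.** **The trigger is inferred.** The text does not say that a covariate enters only if its baseline test is significant, and the sentence could be read as a list of adjustment variables. That is fair, and the 5% entry rate is conditional for this reason. But the sentence follows a plan to test baseline differences and makes the differences themselves the covariates. Even as a list it is open-ended, and adjusting for every listed variable and T0 score is unworkable with 36–40 participants.

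**The supplement may fix the model.** It may. The article nevertheless states a rule of its own, so the point concerns that rule and not an omission. If the supplement already fixes the model, the article should be brought into line with it.

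**The consequence is modest.** This stands. The change score already subtracts T0, and in step 5 the planned power is kept and overall type I error is not inflated. Baseline comparisons use group labels but no outcome data, so the rule cannot be tuned to the result.

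**Stronger readings that the document does not support.**

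- A reader might infer that a failed normality test sends the primary comparison to Mann–Whitney, which yields no mean difference to set against the margin. The article does say "A normality test will be used to assess the distribution of all the outcome measures", but it ties the choice between t-test and Mann–Whitney to baseline comparisons only, and it plans covariates, which Mann–Whitney does not carry.
- A reader might argue that integer MMSE changes will almost always fail a normality test. No test is named, and the failure rate depends heavily on the SD being exactly 1.
- A reader might take 75% as the chance that the primary model is altered. That figure needs independence and counts every secondary T0 score as a candidate for the primary model, so it is an upper bound.

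**Conclusion.** The point holds as a matter of efficiency and prespecification. It is not an error that invalidates the design. As worded, the plan most naturally lets chance imbalance choose the primary model and usually leaves out T0 MMSE and diagnosis.

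The loss is about 2 to 6 percentage points of power against a fixed ANCOVA. In near-miss trials the unadjusted result is also materially biased, in a direction set by which arm starts lower. It would be wrong to infer that the rule inflates the overall false-positive rate or that 18 per group is too few: neither follows when T0 MMSE is the only candidate. Selection from a larger candidate set was not simulated.

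The figures rest on an assumed T0–T1 correlation of 0.3–0.8, equal T0 and T1 variances, normal scores, the planned SD of 1 and an assumed 5% trigger. The case for fixing the two covariates does not depend on the exact values.

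**What to change.** State in Planned Analysis that:

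- The primary analysis is ANCOVA of T1 MMSE (or T1–T0 change) on group, T0 MMSE and diagnosis stratum, fitted whatever the baseline comparison shows, with the confidence limit for the adjusted group difference compared with the 2-point margin.
- Each secondary outcome that has a T0 measurement is adjusted for its own T0 value and for diagnosis stratum.
- Baseline data are presented descriptively, without significance tests used to select covariates.
- Any other covariate set is a labelled sensitivity analysis.

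The cost is a change of wording and one degree of freedom per covariate. Both covariates are already collected, and the planned sample size need not change.

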### Ethical Issues

This study will involve human participants, cognitive rehabilitation interventions, data collection, elaboration, and abstraction used for the evaluation of the two therapeutic options. In addition to ethical approval, all the procedures and the data managed have been approved by the Data Protection Officer of the IRCCS Mondino who guarantees compliance to the GDPR. The information provided when presenting the informed consent to the participants will be given in a language appropriate to the individual level of understanding. Participants will also be encouraged to ask questions before signing the informed consent.

To the best of our knowledge, HomeCoRe should not have any potential negative impact on the participant. The investigator will communicate any possible, unforeseen, and adverse event to the Ministry of Health. With respect to payment policies for participants, the amount of compensation and the method and timing of disbursement must be consistent with the laws, regulations, and guidelines of the region in which this study is conducted and must not improperly influence a decision of the participant to participate. This study is a no-profit study and, in Italy, the national legislation refers that it is forbidden to offer or request any kind of financial benefit for the participation in a clinical experimental trial.

Since participants are expected to interact with a rehabilitation tool (the HomeCoRe application), one possible issue could be frustration in case of lack of ability to cope with that technology. However, this risk will be mitigated, before the beginning of HomeCoRe treatment, thanks to specific training sessions on the use of this application that will be delivered to participants (and possible caregivers) (see CoRe/HomeCoRe software architecture section). Moreover, the interface fully complied with the guidelines for human–computer interaction, to make the user interface as easy as possible.

## Discussion

Due to the increase of the aging population, we are witnessing a steady increase in the number of older adults at risk of developing cognitive decline with a consequent increase of economic burden on healthcare. Therefore, the WHO Global Action Plan on the Public Health Response to Dementia 2017–2025 recommends taking global action against cognitive decline and dementia, encouraging governments worldwide to focus on prevention and improving healthcare services (48). Telemedicine is defined as an interface in a virtual patient–clinician relationship to provide primary and secondary care by adopting innovative solutions reaching larger groups of participants (49). Telemedicine can be considered as an adaptation of the healthcare model based on in-person interaction, according to the characteristics and needs of the participants (50). In particular, TR is a telemedicine subfield aimed at providing rehabilitation at a distance (51). TR provides benefits for the healthcare system, patients, and caregivers in terms of cost-effectiveness and feasibility for large-scale implementations (52–54). It represents a replacement for in-person treatment or its continuation, favoring equitable access to care not only for older patients with dementia or physical disabilities, but also for subjects of working age or living in geographically remote areas in predementia phases. Hence, TR is a unique opportunity in the field of cognitive rehabilitation to guarantee constancy and continuity to cognitive training programs.

The results of this trial will inform about the comparability of HomeCoRe with CoRe system. In case they will result equivalent, such a finding would support the use of HomeCoRe in the treatment of patient at distance, with the consequent multiple positive impacts mentioned above. In this framework, HomeCoRe could be incorporated into clinical routine practices as a complementary non-pharmacological therapy to contrast cognitive impairment and dementia. In case HomeCoRe will prove less effective than CoRe, it would lead to the conception of telerehabilitation as a compromise that must be made under particular conditions such as in case of emergency [i.e. coronavirus disease 2019 (COVID-19) pandemic] or personal needs (e.g., travel difficulties).

